**Fig. 1 Fig1:**
[figure not shown]
Regional variation of aflatoxin exposure by former provinces, Kenya 2007

#### Sample size determination

According to the Kenya Population census of 2009, Siaya County had a population of 842,304 while Makueni County had 884,527 people [39]. The sample size was determined using Krejcie and Morgan’s methodology [40].
$$ s={X}^2 NP\left[1-P\right]\div {d}^2\left[N-1\right]+{X}^2P\left[1-P\right] $$

where *s* is the required sample size; *X*^2^_=_ 3.841, which is the table value of chi-square for 1 degree of freedom at 95% confidence interval; *N* is the population size; *P* is the population proportion which is assumed to be 0.50 since this provides maximum sample size; and *d* is the degree of accuracy expressed as a proportion (0.05).

According to Krejcie and Morgan’s formula, the estimated sample size was determined to be 393 schoolchildren per county [40]. The estimated total number of participants required to achieve the study objectives was 786 across different schools from 2 counties.

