#### Sampling

Makueni is confirmed to have the highest prevalence of AF exposure among Kenya’s 47 counties spread across former 8 provinces. In contrast, Siaya which is considered to be a low exposure region has had few studies conducted in the region. Siaya and Makueni Counties were chosen based on AF exposure levels reported on published literature [20, 25, 37]. Schools were randomly selected per constituency at the county level as long as the school did not have feeding programs and were located at least 3 km from a shopping center to limit the possibility of consuming market or store-bought maize products. In Siaya County, schools allow a 1-h lunch break where students go home for lunch and come back for afternoon classes. In Makueni, however, students bring lunch from home in the morning and have half-hour lunch break, before resuming classes in the afternoon. Participants enrolled in the study were randomly selected using the Kish Grid Method to avoid selection bias [41].

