#### Laboratory and data analysis planned

Dietary exposure to AFs can be estimated by quantifying contamination levels in food samples, estimates from dietary intake surveys, and food frequency questionnaires. However, the heterogenous nature of AF contamination in food products does not provide accurate measurement of personal exposures. Therefore, in addition to estimating AF contamination in foods, combinations of AF biomarkers either in blood serum, plasma, tissues, or urine are recommended for studies to determine actual exposure in human sub-populations [42, 43]. Once ingested, AFs undergo metabolism and their metabolites are known to irreversibly bind to protein albumin to form AFB_1_-lysine adducts which are validated biomarkers of AF exposures [44, 45]. Laboratory analyses of this study are currently ongoing, and the study timeline is summarized in Table 1. In addition to quantification of AFB_1_-lysine adducts in serum samples and total AFs in household maize products, plans are underway to quantify other AF metabolites in urine using High Pressure Liquid Chromatography with Fluorescence Detection [44, 45]. STATA15 (College Station, TX), SAS v9.4 (Cary, NC), and R (Vienna, Austria) will be used in adjusting for socioeconomic factors and other possible confounding variables to model data that is likely to associate AF exposure to adverse health outcomes.

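### The 0.05 accuracy per county comes from a simple-random-sampling formula, but children are sampled through schools, so at P = 0.50 it holds only if within-school correlation is practically zero

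*Protocol article*

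**What the plan says.** The section *Sample size determination* gives the whole calculation. The chi-square value is "3.841, which is the table value of chi-square for 1 degree of freedom at 95% confidence interval". P "is the population proportion which is assumed to be 0.50 since this provides maximum sample size". The term d "is the degree of accuracy expressed as a proportion (0.05". For N it reports that "Siaya County had a population of 842,304 while Makueni County had 884,527 people". From these, "the estimated sample size was determined to be 393 schoolchildren per county", and the number of "participants required to achieve the study objectives was 786 across different schools from 2 counties". No design effect, ICC or number of schools appears in the calculation.

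The section *Sampling* describes how the children were reached: "Schools were randomly selected per constituency at the county level as long as the school did not have feeding programs". Participants were then chosen with the Kish grid. *Methods/design* also describes random selection of schools in different constituencies of each county.

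On analysis, *Laboratory and data analysis planned* says that three software packages "will be used in adjusting for socioeconomic factors and other possible confounding variables to model data that is likely to associate AF exposure" to adverse outcomes. It says nothing about how variances will be estimated. It neither provides for school clustering nor rules it out.

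**The concern.** The size formula and the sampling scheme describe two different designs. The formula assumes that individuals are drawn independently from the county population. The scheme draws schools first and children within them. If children at the same school resemble each other, 393 of them carry less information than 393 independent children, and the printed accuracy is too optimistic.

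The document gives reasons to expect some resemblance. Maize is grown on subsistence farms and eaten untested (*Background*). Schools were placed at least 3 km from a shopping center so that children would eat local rather than bought maize (*Sampling*). Awareness programs, diet diversification and food security may differ between the areas of recruitment (*Study limitations*).

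Two things are at stake. The first is the precision of each county's prevalence estimates. The second, if schools were left out of the analysis, is the validity of the Makueni versus Siaya comparison, which is the study's main hypothesis. Every school lies wholly in one county, so the full design effect falls on that contrast.

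**Working it through.** **Inputs from the protocol** (*Sample size determination*): X² = 3.841, P = 0.50, d = 0.05, N = 842,304 (Siaya) and 884,527 (Makueni), stated n = 393 per county.

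**Assumed inputs:** m = 10 to 40 sampled children per school and ICC = 0.01 to 0.10. The text gives neither. The recruitment flow diagram (Fig. 2) could not be read for this check.

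**Step 1: reproduce the stated size.** With the denominator bracketed as the formula intends,

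s = X²·N·P(1−P) / [d²(N−1) + X²·P(1−P)]

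- Siaya: 3.841 × 842,304 × 0.25 / (0.0025 × 842,303 + 0.96025) = 383.93, so 384.
- Makueni: the same formula also gives 383.93, so 384.

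The stated 393 is 9 children (2.3%) above 384. It is essentially the simple-random-sampling figure.

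**Step 2: how much clustering 393 can absorb.** The simple-random half-width at n = 393 is sqrt(3.841 × 0.25 / 393) = 0.0494. The largest design effect that still meets 0.05 is 393 / 383.93 = 1.024. With DEFF = 1 + (m−1)·ICC, the largest admissible ICC is 0.0236 / (m−1):

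- m = 10: 0.0236 / 9 = 0.0026
- m = 20: 0.0236 / 19 = 0.0012
- m = 40: 0.0236 / 39 = 0.0006

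**Step 3: precision and test size under assumed clustering, at P = 0.50.**

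- Effective n = 393 / DEFF.
- Half-width = sqrt(3.841 × 0.25 × DEFF / 393).
- Type I error of a nominal 5% county test that ignores schools = 2·[1 − Φ(1.96 / sqrt(DEFF))].

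| m | ICC | DEFF | Effective n per county | 95% half-width (points) | Type I error if schools ignored |
|---|---|---|---|---|---|
| 10 | 0.01 | 1.09 | 361 | 5.2 | 6.0% |
| 20 | 0.02 | 1.38 | 285 | 5.8 | 9.5% |
| 20 | 0.05 | 1.95 | 202 | 6.9 | 16% |
| 40 | 0.05 | 2.95 | 133 | 8.5 | 25% |
| 40 | 0.10 | 4.90 | 80 | 10.9 | 38% |

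**Step 4: proportions other than 0.50.** P = 0.50 is the worst case. As an illustration, take P = 0.78, the share of archived sera with detectable aflatoxin in the survey cited under *Justification of Makueni and Siaya Counties as study sites*. The simple-random half-width is sqrt(3.841 × 0.78 × 0.22 / 393) = 0.041, so a design effect up to (0.05 / 0.04095)² ≈ 1.49 still meets 0.05. At P = 0.10 or 0.90 the limit is 0.0025 × 393 / (3.841 × 0.09) ≈ 2.8.

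**The case against.** The strongest reply is that the size of the loss is unknown and may be small. The document also describes exposure at household level: each household stores its own maize, lunches come from home, schools with feeding programs are excluded, and contamination is called heterogeneous. The regional contrasts it cites are between provinces and counties, not between schools within a county. With 10 children per school and an ICC of 0.01 the half-width is 5.2 points, hardly different from 5. Away from P = 0.50 there is further slack. All of this stands, and it is why the figures are given as a range under assumptions. It does not restore the printed accuracy at the printed P, which needs an ICC of about 0.003 or less.

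Three stronger readings are tempting, and the document does not support them.

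- A reader might infer that standard errors will be too small because the analysis ignores schools. The protocol makes no such commitment. Its one analysis sentence names software and confounder adjustment, and variance estimation may be set out in the full plan. The type I error figures are therefore conditional.
- A reader might apply the same design effects to the regressions of outcome on the individual biomarker. There the inflation depends on how far both exposure and outcome cluster by school. It is unknown and usually smaller.
- A reader might treat constituency as a further stage of clustering. Selection of schools per constituency reads as stratification, which can recover a little precision but would not normally cancel the effect of schools.

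**Conclusion.** The mismatch between formula and design is established. The 0.05 accuracy is a simple-random-sampling property, 393 contains no usable allowance for clustering, and the sample is drawn by school. At P = 0.50 the accuracy is not delivered for any ICC above roughly 0.001 to 0.003 with 10 to 20 children per school.

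The size of the shortfall cannot be computed from the document. Under the assumed 10 to 40 children per school and ICC of 0.01 to 0.10, the half-width is about 5.2 to 10.9 points at P = 0.50. For proportions nearer 0 or 1 a modest design effect may still meet 0.05.

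The consequence for testing is a warning, not a demonstrated error. If schools were ignored, the county comparison would have a true type I error of about 9.5% to 38% for design effects of 1.38 to 4.90. These figures apply to county estimates and the county contrast only.

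**What to change.** - Keep 393 per county. Sample collection is described in the past tense, and the point concerns the stated precision and the analysis, not recruitment.
- Restate the accuracy as about 0.05 × sqrt(DEFF) at P = 0.50, using the actual number of schools and children per school and a range of ICCs.
- State that county estimates, the Makueni versus Siaya comparison and the exposure-outcome regressions treat school as the cluster. Either a school random intercept or survey estimation with school as primary sampling unit and constituency as stratum would serve.
- Add a few-clusters correction if the number of schools is small.

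The cost is wording and analysis code, with no additional children. Laboratory work is described as ongoing, so this can still be fixed before results are known. The downside is a less favourable stated precision and wider intervals.

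### The stated sample size of 393 per county (786 in total) is not what the printed formula and inputs give: 384 per county, 768 in total

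*Protocol article*

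**What the plan says.** The section Sample size determination of the Protocol article takes its population sizes from the 2009 census: "Siaya County had a population of 842,304 while Makueni County had 884,527 people". It names Krejcie and Morgan's method, prints the formula and defines each term:

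- X² is "3.841, which is the table value of chi-square for 1 degree of freedom at 95% confidence interval".
- P "is the population proportion which is assumed to be 0.50 since this provides maximum sample size".
- d, the accuracy, is set at 0.05.

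The section then credits the result to the formula: "the estimated sample size was determined to be 393 schoolchildren per county". It closes with the sum over both counties: "The estimated total number of participants required to achieve the study objectives was 786 across different schools from 2 counties".

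No other adjustment is mentioned there. The section has no allowance for non-response, attrition, clustering by school or rounding.

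**The concern.** The method is closed-form and every input is printed, so the result can be checked by hand. A reader who does so gets 384, not 393. The two stated figures agree with each other (2 × 393 = 786), so this is not one garbled digit in the text.

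These are the only sample-size figures in the article, and they are presented as what the study needs. If they do not follow from the stated basis, a reader cannot tell whether the arithmetic slipped, an input differs from the one printed, or a margin was added without being reported.

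**Working it through.** **Inputs**, all from Sample size determination:

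| Term | Value |
|---|---|
| X² (1 df, 95%) | 3.841 |
| P | 0.50, so P(1 − P) = 0.25 |
| d | 0.05, so d² = 0.0025 |
| N, Siaya | 842,304 |
| N, Makueni | 884,527 |
| Stated result | 393 per county, 786 in total |

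**Formula**, with the denominator bracketed as the method intends:

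s = X²·N·P(1 − P) / [d²(N − 1) + X²·P(1 − P)]

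The constant X²·P(1 − P) is 3.841 × 0.25 = 0.96025.

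**Attempt to reproduce 393**

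- Siaya: 0.96025 × 842,304 / (0.0025 × 842,303 + 0.96025) = 808,822.4 / 2,106.718 = 383.93, which rounds up to 384.
- Makueni: 0.96025 × 884,527 / (0.0025 × 884,526 + 0.96025) = 849,367.1 / 2,212.275 = 383.93, which rounds up to 384.
- Total: 2 × 384 = 768, against the stated 786.

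**Could another population size give 393?** No. Because 0.96025 is larger than 0.0025, s rises with N towards the limit 0.96025 / 0.0025 = 384.1. Using only school-age children as N would lower the result. Pooling the two counties (N = 1,726,831) gives 384.01.

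**Could another reading of the method give 393?**

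| Variant | Result |
|---|---|
| Denominator taken as d²(N − 1) alone, last term added afterwards | 385.06 |
| z = 1.96 squared, infinite N | 384.16 |
| z = 2 squared, infinite N | 400 |
| Yamane's formula | 399.8 |

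None returns 393.

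**What would give 393?** Any one of these:

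- d = √(0.96025 / 393) = 0.0494 instead of 0.05;
- X² = 393 × 0.0025 / 0.25 = 3.93 instead of 3.841;
- an inflation of about 2%: 393 / 384 = 1.023, or for example 385 / 0.98 = 392.9.

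The first two contradict the printed values, and the third is not stated.

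**Size of the gap:** 393 − 384 = 9 per county and 786 − 768 = 18 in total; 18 / 786 = 2.3%.

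**The case against.** The strongest reply is that nothing is lost. The stated number is larger than the formula requires, so the margin of error is slightly better than planned (0.0494 against 0.05), and no estimate, test or conclusion changes. The article also describes recruitment in the past tense and sets no rule tying the end of recruitment to 786, so a correction would not alter how the study was run. All of this stands, and it limits the weight of the point.

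A second reply is that the article condenses a fuller protocol, where a margin of about 2% may be recorded. That is possible, but it does not rescue the text. The sentence presents 393 as the formula's own output, so if a margin was added, the sentence is still wrong.

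The cause cannot be settled from the article. The correct total, 768, and the stated total, 786, differ by a swap of the last two digits, and half of 786 is 393, so a transposition is plausible. An unreported margin would fit as well. The finding does not depend on which is true.

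The missing bracket in the printed denominator is a separate typographical matter. Reading the formula without it gives 385.06, so it does not explain 393.

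**Conclusion.** The point holds. With the printed formula and inputs, the sample size is 384 per county and 768 in total. The stated 393 and 786 lie above the highest value those inputs can give (384.1 per county for any population size, or 385.06 if the denominator is misread). The discrepancy is 9 children per county, 18 in total, about 2.3%, in the conservative direction.

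This rests only on the values printed in the section and on the standard bracketing of the named method. It is an error of statement that should be corrected. It is not evidence that the study is too small for the precision it set itself.

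**What to change.** Establish which number was actually planned, then restate the result in one of two ways:

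- If 393 arose from an arithmetic or typing slip, give 384 per county and 768 in total.
- If 393 and 786 were the working targets, write that the formula requires 384 per county (768 in total), that 393 per county (786 in total) were targeted, and why the margin was added.

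In either case print the formula with its denominator bracketed: s = X²NP(1 − P) / [d²(N − 1) + X²P(1 − P)].

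The cost is one sentence and one formula. Enrolment and analysis are unaffected.

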#### Sampling

Makueni is confirmed to have the highest prevalence of AF exposure among Kenya’s 47 counties spread across former 8 provinces. In contrast, Siaya which is considered to be a low exposure region has had few studies conducted in the region. Siaya and Makueni Counties were chosen based on AF exposure levels reported on published literature [20, 25, 37]. Schools were randomly selected per constituency at the county level as long as the school did not have feeding programs and were located at least 3 km from a shopping center to limit the possibility of consuming market or store-bought maize products. In Siaya County, schools allow a 1-h lunch break where students go home for lunch and come back for afternoon classes. In Makueni, however, students bring lunch from home in the morning and have half-hour lunch break, before resuming classes in the afternoon. Participants enrolled in the study were randomly selected using the Kish Grid Method to avoid selection bias [41].

#### Human participants

School administrations were requested to convene parent meetings at a convenient time and location for participants. Community leaders including local area chiefs and members of the county assembly were invited to the meetings. The chairperson of the Parent Teachers Association was in attendance and presided over the meetings. The study purpose and significance were explained to school officials, teachers, support staff, and parents. The participants were given ample opportunity to ask questions during the meeting, before subject recruitment, and during the study to ensure full disclosure of study components. Informed consent forms were explained to parents in their local dialect, and all their questions were addressed before being asked to provide consent and fill out questionnaires.

The five-part questionnaire administered collected basic information including participants’ age, sex, weight, height, and mid-upper arm circumference; sociodemographic factors including marital status, education levels, living conditions, occupations of both the respondent and their spouse, household income levels, and information on home ownership and living conditions. Participants also reported farming practices which entail whether they grow or buy maize for household use, use of pesticides and/or fertilizers during farming, extent of AF knowledge, and how each household stores maize and other food supplies after harvest. In addition, the questionnaire collected information on dietary intake of different food groups, number of meals in a day, food choice, and nutrition practices. Information collected from questionnaires provided sufficient information to enable analysis of socioeconomic status and respective poverty levels. Moreover, these possible confounding factors can be easily controlled in statistical analyses.

After the meeting at various schools, the researchers crosschecked all consent forms and questionnaires for accuracies. In cases where consent was not clear, the individual parent was contacted to confirm their decision. In addition, parents were required to provide additional consent by checking YES or NO on the questionnaire form to allow international shipping of samples, use of media files, storage of biospecimens, and publication of anonymized data summaries. Parents were also asked to provide about 150 g of household maize flour or kernels for AF measurements of household food. Only healthy children between the ages of 6 and 12 with no current active medication were enrolled in the study. After obtaining assent, the study personnel obtained anthropometric measurements including height, weight, and mid-upper arm circumference; 6–8 ml of venous blood; and 15 ml of urine samples. Collection of urine samples was discontinued due to budget constraints and the labor-intensive nature of collecting urine from children. Figure 2 shows a flow diagram showing the study participants’ recruitment and enrollment.

**Fig. 2 Fig2:**
[figure not shown]
Study participants’ recruitment

#### Laboratory and data analysis planned

Dietary exposure to AFs can be estimated by quantifying contamination levels in food samples, estimates from dietary intake surveys, and food frequency questionnaires. However, the heterogenous nature of AF contamination in food products does not provide accurate measurement of personal exposures. Therefore, in addition to estimating AF contamination in foods, combinations of AF biomarkers either in blood serum, plasma, tissues, or urine are recommended for studies to determine actual exposure in human sub-populations [42, 43]. Once ingested, AFs undergo metabolism and their metabolites are known to irreversibly bind to protein albumin to form AFB_1_-lysine adducts which are validated biomarkers of AF exposures [44, 45]. Laboratory analyses of this study are currently ongoing, and the study timeline is summarized in Table 1. In addition to quantification of AFB_1_-lysine adducts in serum samples and total AFs in household maize products, plans are underway to quantify other AF metabolites in urine using High Pressure Liquid Chromatography with Fluorescence Detection [44, 45]. STATA15 (College Station, TX), SAS v9.4 (Cary, NC), and R (Vienna, Austria) will be used in adjusting for socioeconomic factors and other possible confounding variables to model data that is likely to associate AF exposure to adverse health outcomes.

**Table 1 Tab1:**
[figure not shown]
Study timeline

## Discussion

This is the first study designed to establish a baseline AF exposure in children between the ages of 6 and 12 years. To date, studies to establish AF exposure have been completed in populations of children below the age of 5 years, adults between the ages of 18 and 65 years, vulnerable populations of pregnant women, and immunocompromised groups including individuals suffering from HIV/AIDS and hepatitis B virus [6, 12, 46, 47]. Moreover, these studies tend to address specific adverse health outcomes including immune suppression, micronutrient levels, possible growth impairment, and risks of carcinogenesis without controlling for related outcomes. For instance, studies aimed to assess the effect of AF exposure on children’s growth in Benin and Togo prioritized possible growth impairments and micronutrient levels in blood plasma while immune markers were not evaluated [48, 49]. Conversely, a study in Ghana prioritized evaluation of immune suppression as it relates to AF exposure while neither micronutrient markers nor growth indicators were considered [50]. Studies in farm animals and human sub-populations have reported downstream effects associated with AF exposure, malnutrition, immune suppression, vulnerability to infectious diseases, and consequently growth impairments [10, 12, 51]. Intervention studies such as use of enterosorbents like Novasil Clay to bind AF adducts in human blood have been evaluated for safety, palatability, and efficacy [52–55]. In a phase II clinical trial, 180 adults aged 18 to 58 years at risk of aflatoxicosis who received Novasil Clay capsules significantly had lower AFB_1_-lysine adducts in both blood and urine samples in a dose-dependent manner [55]. Other interventions involving use of green tea polyphenols [56] and chlorophyllin [57] have been shown to reduce AF biomarkers and may also form basis for future prospective studies. The current study protocol provides a multifaceted approach in addressing adverse health outcomes linked to dietary exposure to AFs while controlling for social, economic, and demographic factors. While the mechanism by which AFs contribute to adverse health outcomes is currently unknown, it is suspected to be biological [58].

Given the multifaceted aspects of this study, lessons that may be valuable to other scientists seeking to undertake research projects in low- or middle-income countries are outlined herein. First, plan the study at least 2 to 3 years in advance before actual fieldwork to give you and your team sufficient time to prepare, apply for ethics justification, follow up different requirements, and obtain additional permissions required to conduct field studies involving human subjects. Our study’s ethical approval was prolonged because it involved children.

In addition, travel to your country of interest to build social capital. Moreover, foreign scientists are likely to be more successful if they work collaboratively with local scientists in low- and middle-income countries. It is also important to familiarize oneself with myths and beliefs in a community as blood draw is a contentious issue in some communities. In our study populations, a common belief that blood products can used for financial profit by researchers was prohibitive. Moreover, study administrators must make it clear to participants that their samples will be shipped for analysis to a different location and obtain consent for shipment which must be approved a priori by the ethics committee. The paperwork associated with additional approvals for sample shipment, export, and import can be extensive and thorough. Last but not least, remuneration of field workers can exponentiate overhead costs.

